**Figure 2 figure2:**
[figure not shown]
A screenshot of the Condom-Him intervention study.

### Control Arm

The control arm involves links to various websites that address standard information HIV/acquired immunodeficiency syndrome (AIDS). Participants in the control group are invited to view this list of predetermined websites at their convenience.

### Sample Size

Because of the pre-experimental nature of the proposed pilot RCT study, we aim to achieve a sample size of 60 with 30 participants per group. The sample size calculation is based on the rule of 10 cases per independent variable included in the analysis [12]. A convenience sample of participants will be randomly assigned either to the experimental arm (Condom-Him) or to the control arm, which includes a list of various websites providing information relating to HIV/AIDS.

### Planned Inclusion Criteria

Individuals will be selected to participate in the study if they meet the following preset inclusion criteria: (1) 18 years of age or older, (2) HIV-positive, (3) MSM, (4) engage in unprotected anal intercourse with a partner who is HIV-negative or whose HIV infection status is unknown, (5) read English, and (6) have access to a computer and the Internet.

### Participant Recruitment

A two-pronged approach will be used to recruit participants. The first method of recruitment will use Internet-based methods (ie, advertisement in chat rooms, online classified advertisements, social media such as Facebook and Twitter, and links to the intervention website posted within various HIV/AIDS community center websites). The second method of recruitment will use offline strategies (ie, flyers and brochures will be posted in various community sexual health clinics). In addition, advertisements in local newspapers will be used to aid in participant recruitment. Participants interested in the study will be directed to the study website where further information about the study will be provided via a video. The interested participants will be asked to complete a Web-based consent form. The consent form will provide information relating to the study in addition to telephone numbers and email addresses of the research staff for further questions before consenting to participate.

### Random Assignment

Eligible consenting participants will be randomly assigned either to an experimental group (Condom-Him) or to a control group (list of websites with various HIV/AIDS information). The participant assignment protocol will be based on a ratio of 1:1, which will be performed using a computer program. The computer program will automatically allocate participants randomly to the experimental or control groups. Because of the automatic nature of the allocation process, direct exposure to the treatment allocation process by any members of the research team is eliminated.

### Measurements

All measurements are self-administered online. The data that is collected online will be stored on a secure server located at the Research Chair, Centre Hospitalier de l’Université de Montreal.

### Sociodemographic Characteristics

Standard questions will be used to record age, level of education, and sexual history such as date of HIV-positive result, current involvement in treatment, current viral load count, type of partner (casual/primary partner), perceived status of the partner (positive, negative, or unknown), and previous exposure to any sexually transmitted diseases.

### Self-Efficacy

The self-efficacy for condom use measure contains a set of items to rate the belief of participants that within the next 6 months, they will be able to use condoms every time they have anal sex in different situations with a partner who is HIV-negative or whose HIV infection status is unknown. A 4-point response scale, which ranges from “strongly agree” (0) to “strongly disagree” (4) is used. The psychometric properties of the measure show good internal consistency; Cronbach alpha=.96 [13].

### Intention to Use Condoms

To measure the intention of the participants to use condoms, participants are asked three questions about their intentions over the next 6 months to use a condom. The scale is a 2-point response (“certainly not”/“yes certainly”). The psychometric properties of the measure show good internal consistency; Cronbach alpha=.89 [13].

### Condom Use

To determine condom use, the participants are asked the following question “In the past 2 weeks, thinking about the times you had anal sex with a regular or casual male partner, what percentage of times did you use a condom with someone who was HIV-negative or of unknown status”? This measure showed acceptable psychometric properties [13].

### Acceptability of Condom-Him

The Treatment Acceptability Measure Used for Hiv Prevention Interventions [14] Contains a Set of Items for the Participants to Rate the (1) Appropriateness and Suitability of the Intervention to Assist With Increasing Condom Use, (2) Effectiveness of the Intervention in Helping Them Increase Their Condom Use, and (3) Convenience (ie, Ease of Implementation) and Willingness to Comply With the Intervention Strategies/activities. We Used a 4-Point Response Scale, Which Ranged From “not At All” (0) to “very Much” (4). High Scores Reflect a Positive or Favorable Appraisal of the Intervention. the Psychometric Properties of the Measure Show a Good Internal Consistency; Cronbach Alpha=.86 [15]. in Addition, the Measure Contains Two Qualitative Questions Asking Participants to Indicate “what Makes This Intervention Most and Least Appealing”.

### Feasibility of Condom-Him

The feasibility of the Internet-based intervention will be measured through the recruitment and retention rates, duration of intervention participation, and need for prompts or reminders to complete the post-test questionnaire.

### Utilization of Condom-Him

The utilization of the Internet-based intervention will be measured on the basis of the length of time the participant spent in completing the single session.

### Analysis

#### Preliminary Analysis

Descriptive statistics will be used to characterize the participants in terms of a sociodemographic profile. We will examine the distribution of these variables for normality, which is required for subsequent statistical analyses.

#### Analysis to Address Study Objectives

Independent *t* tests will be used to examine the differences between the control and experimental groups in terms of the participants’ self-efficacy, intention to use condoms, and actual condom use before the intervention and 2 weeks after the intervention.

Descriptive statistics will be used to examine the acceptability rating of the intervention. In addition, qualitative responses of the participants to open-ended questions about what they find most and least appealing about the Condom-Him will be analyzed to identify the strengths and weaknesses of the intervention as perceived by the participants. Recruitment and retention rates for the control and experimental groups will be used to determine the feasibility of the intervention and online data collection methods. Lastly, descriptive statistics will be used to examine the utilization of the intervention.

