## Methods

### Study Design

The design of the proposed pilot study to evaluate the acceptability and feasibility and acceptability of the tailored Internet-based intervention in increasing condom use among HIV-positive MSM is a randomized controlled parallel-group superiority trial (NCT01726153). The flow of participants within the randomized control trial is shown in Figure 1. Participants will be randomly assigned using a one-to-one allocation ratio. Random assignment will occur only after participants have completed baseline questionnaires. The random assignment will be performed by the computer system that has been programmed by the computer/Web-intervention programmer. Participants cannot be blinded to their assigned arm. Individuals within the control arm receiving a list of various websites will be aware they have not been allocated to use the tailored Internet-based intervention. Participants in the experimental arm (Condom-Him) will be aware that they have been allocated to use the tailored Internet-based intervention. The researcher will be blinded to the participant’s treatment assignment. The research assistant, who will be downloading the data, will be the only individual aware of the participant’s assignment. The research assistant will not have any participation in the random assignment of participants because this process does not involve any individuals and is entirely performed using the computer program. The outcomes of the study will be collected at two time points: pre-intervention (T0) and two weeks after intervention (T1). The participants will be sent an email two weeks after the intervention to remind them to revisit the study website to complete the post-test questionnaires. The study has been approved by the research ethics board of both the academic and research institutions.

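### The 2-week t tests leave out each outcome's own pre-randomisation value; adjusting for it would sharpen the efficacy estimates at almost no cost, and the baseline t tests serve no purpose

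*Protocol article*

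**What the plan says.** The section Analysis to Address Study Objectives gives the only between-arm efficacy analysis in the article. Independent t tests compare control and experimental participants on self-efficacy, "intention to use condoms, and actual condom use before the intervention and 2 weeks after the intervention". No covariate, change score or regression model is named. The plain reading is one between-arm test per outcome at each of two times.

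Study Design states that the outcomes are measured before the intervention (T0) and two weeks after it (T1). It adds: "Random assignment will occur only after participants have completed baseline questionnaires". The T0 values are therefore true pre-randomisation covariates.

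On size, the Sample Size section says "we aim to achieve a sample size of 60 with 30 participants per group". On allocation, Random Assignment says: "The participant assignment protocol will be based on a ratio of 1:1, which will be performed using a computer program". No stratification on the baseline outcomes is described.

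**The concern.** Two things look wrong.

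- **The T0 tests.** Both arms are the same randomised population before anyone is treated, so any difference is due to chance. The null hypothesis is known to be true, and the p-value informs no decision.
- **The T1 tests.** The score a person gave two weeks earlier on the same measure is likely to be among the best predictors of the follow-up score. Leaving it out keeps explainable variation in the error term. It also leaves the estimate exposed to whatever baseline difference the allocation happened to produce.

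What is at stake is the quality of a preliminary estimate. Efficacy on self-efficacy and intention is a secondary objective. However, the introduction also names increased condom use as the primary outcome, and the Results section says the findings will enable the design of a larger trial. A noisier or shifted estimate would carry into that design.

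**Working it through.** **The plan's own figure.** The Sample Size section says: "The sample size calculation is based on the rule of 10 cases per independent variable included in the analysis". The number of variables is not given. Working back, 60/10 = 6 variables on the total, or 30/10 = 3 per arm, whereas a two-group t test has one independent variable. With no alpha, power, effect size or SD stated, 60 cannot be reproduced. It is used below only as n = 30 per arm.

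**Assumptions not in the article.** Two-sided alpha 0.05; a true effect of 0.5 SD; r = 0.3, 0.5 and 0.7; roughly normal outcomes; 30 completers per arm.

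**Step 1: size of chance imbalance.** SE of the baseline difference = sqrt(2/30) = 0.258 SD.
- Median absolute imbalance: 0.674 × 0.258 = 0.17 SD.
- P(over 0.25 SD) = 33%; P(over 0.4 SD) = 12%; P(over 0.5 SD) = 5%.

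**Step 2: how much reaches the 2-week estimate.** The expected shift is r × imbalance.
- A 0.3 SD imbalance shifts the unadjusted difference by 0.3 × 0.3 = 0.09, 0.5 × 0.3 = 0.15 or 0.7 × 0.3 = 0.21 SD.
- The median imbalance of 0.17 SD shifts it by about 0.09 SD at r = 0.5.

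**Step 3: precision.** Adjustment multiplies the residual variance by 1 − r², so the equivalent sample-size factor is 1/(1 − r²). The detectable effect at 80% power is the t-test value, 0.736 SD, times sqrt(1 − r²). Power comes from the noncentral t distribution.

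| Analysis | 1 − r² | Sample-size factor | Detectable effect (80% power) | Power for 0.5 SD |
|---|---|---|---|---|
| T1 t test | – | 1.00 | 0.74 SD | 48% |
| Adjusted, r = 0.3 | 0.91 | 1.10 | 0.70 SD | 51% |
| Adjusted, r = 0.5 | 0.75 | 1.33 | 0.64 SD | 59% |
| Adjusted, r = 0.7 | 0.51 | 1.96 | 0.53 SD | 76% |

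A simulation of 40,000 trials per value of r gave power of 48% for the t test and 51%, 59% and 75% for the adjusted analysis.

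**Step 4: type I error.** In the same simulation with no effect, both analyses rejected in about 5% of all trials. Among the roughly 12% of trials with a baseline imbalance above 0.4 SD, the t test rejected in 8%, 14% and 22% (r = 0.3, 0.5, 0.7). The adjusted analysis stayed at about 5%.

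**Step 5: the T0 tests.** Three tests at 5% on true null hypotheses give 1 − 0.95³ = 14% chance of at least one significant imbalance if they are independent.

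**The case against.** The strongest reply is that the planned test is sound. A 2-week comparison between randomised arms is unbiased, and its standard error already allows for chance imbalance. That stands. A reader might infer that the planned result is biased, or that a baseline difference passes into it in full. Neither follows: only about r times the difference passes through, and the bias exists only conditionally on the imbalance that occurs.

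The gain also rests on an unknown r. Low values are plausible for condom use, which is a single item covering two weeks, asked of men selected for unprotected intercourse; that may narrow the baseline range. At r = 0.3 the power gain is about 3 percentage points. The Discussion calls retention a concern, so 30 completers per arm is optimistic. These points stand, and they are why the low end must be shown.

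Adjustment is not wholly free for condom use. The item asks for a percentage over the past two weeks with partners who are HIV-negative or of unknown status, while Planned Inclusion Criteria sets no two-week window. Someone with no such act has no defined T0 percentage, and a complete-case adjusted model would drop him although the T1 t test would not. This stands and is handled in the fix.

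Three further inferences are tempting but unsupported:
- That the effect will be judged by setting the before and after p-values side by side. Nothing in the text says so, and no decision is tied to the T0 tests.
- That the outcome distributions will go unchecked. Preliminary Analysis says "We will examine the distribution of these variables for normality, which is required for subsequent statistical analyses", and read literally this covers the sociodemographic variables. But assumption checks are a detail that a condensed article may leave to the full plan.
- That change scores are meant. None is named. A change score would in any case be less precise than adjustment at every r examined, and less precise than the T1 score alone when r is below 0.5.

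**Conclusion.** The point holds as a recommendation on efficiency and on protection against chance imbalance; it does not show that the planned test is invalid. The article fixes an unadjusted comparison as its efficacy analysis although the right covariate is collected before randomisation. Under the assumptions above, the loss equals working with about 91%, 75% or 51% of the information available (r = 0.3, 0.5, 0.7), and it is near nil as r approaches 0. The baseline tests are uninformative rather than harmful. Because this is a pilot with acceptability and feasibility as its primary objective, no confirmatory claim depends on the change. It is still worth making, because it costs little and the estimates are meant to inform a larger trial.

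**What to change.** - Replace the 2-week t tests with one model per outcome: T1 score on arm and the T0 score of the same outcome. Report the adjusted difference with a 95% CI, using robust or bootstrap standard errors because the outcomes are bounded.
- Delete the T0 t tests and show baseline values descriptively by arm.
- For condom use, state in advance that participants with no defined T0 percentage stay in the model, through a missing-baseline indicator or mean imputation of the baseline covariate.

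The cost is about one degree of freedom per model, that one handling step, and rewording of the analysis section. No new data are needed and nothing changes for participants.

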## Results

The results of this pilot study will enable researchers to understand the feasibility, acceptability, utilization, and preliminary efficacy of the Condom-Him Internet-based intervention in increasing condom use for HIV-positive MSM. In addition, the results of this study will highlight the possibilities and potential challenges inherent in Internet-based intervention research. Further, our results will enable designing of a larger RCT to determine the effectiveness of the Condom-Him Internet-based intervention. Rosser et al [6] showed that in countries with high Internet penetration, Internet-based interventions appear to be the most promising approaches for prevention of HIV infection. The Internet-based intervention could provide a cost-effective and widely accessible strategy for prevention of HIV infection, particularly in HIV-positive MSM, a population that has been under served and yet represents a high-risk group for transmitting HIV through unprotected anal intercourse. Our RCT has been funded, and we have started the recruitment and intervention phase. Results of the pilot RCT are expected in September 2013.

## Discussion

Our proposed study protocol has some limitations. The accuracy of self-reporting may be a cause of concern when dealing with reports of sexual practices. However, previous studies indicate that participants report higher rates of sexual practices when completing Internet-based questionnaires than those of a paper-pencil format. This may be because of the nature of anonymity provided by the Internet-based questionnaires. Further, an Internet-based intervention may perpetuate a divide between those who regularly use a computer and have access to the Internet and those who do not. The recruitment methods proposed in the protocol outline methods that use both online and offline strategies. These strategies aim to minimize the divide in recruiting only those participants that regularly use a computer and the Internet. Participants interested in participating in the study may do complete the Internet-based questionnaire at their convenience. Retention of participants is often a concern with Internet-based interventions. To minimize the loss of participants to follow-up, a friendly email is automatically sent to the participant 2 weeks after the intervention as a reminder to visit the Internet-based intervention to complete the post-test questionnaire. In addition, the participants are notified that if a problem occurs, they are able to contact the research team via email or telephone for help with accessing the Internet-based intervention. Data security is often a concern with Internet-based interventions. Within this study, the data collected are stored on a server, which is located within one of research centers of the affiliated universities. The server is managed by an extensive information technology team with firewalls built into the system. The data are only accessible to the researcher and one information technology expert on the research team. The data collected are coded and downloaded into SPSS for further analysis. Subsequently, the data on the server are removed and destroyed.

## Abbreviations

AIDS: acquired immunodeficiency syndrome
CBIs: computer-technology-based interventions
HIV: human immunodeficiency virus
MSM: men having sex with men
RCT: randomized controlled trial
